**Components**

Subjects: Retrospective cohort with serum phosphate recorded between 2005-2015

Setting: Primary Care dataset: RCGP-RSC cohort

Intervention: Serum phosphate measurements during the observation period

Outcome measure 1: Composite cardiac (atherosclerosis) cardiovascular disease outcome measure of primary myocardial infarction; acute coronary syndrome; revascularisation procedure.

Outcome measure 2: Individual cardiac (atherosclerosis) cardiovascular disease outcome measures: primary myocardial infarction; acute coronary syndrome; revascularisation procedure.

Outcome measure 3: Broader individual non-cardiac (atherosclerosis) cardiovascular disease outcome measures: ischaemic stroke; peripheral vascular disease; vascular dementia.

**Background**

Phosphate has many biochemical roles within the body. High serum phosphate predicts cardiovascular events in patients with chronic kidney disease, whilst low serum phosphate may be associated with risk reduction [1]. An association between cardiovascular events and elevated serum phosphate has also been reported in those with coronary artery disease [2], and also among the general population [3, 4, 5]. However, the precise molecular roles of phosphate in conjunction with cardiovascular risk factors are uncertain [1], and phosphate is yet to become an established marker or risk factor for cardiac events. Importantly, as vitamin D and calcium homeostasis overlap with phosphate regulation, the association of these minerals (plus parathyroid hormone) with the three outcomes will be investigated jointly. There is literature evidence that excess calcium and phosphate or their dysregulation may promote calcification during atherosclerosis [7].

The scope of this study aims to evaluate relationships between serum phosphate and the outcome measures. These outcome measures include two groups of cardiovascular events and we intend to examine them separately as follows:

Cardiovascular events due to atherosclerosis

Cardiac events (Outcomes 1 & 2) Non-cardiac events (Outcome 3)

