**Research question**

Is serum phosphate an independent predictor of new atherosclerotic cardiovascular disease events in patients stratified by renal function?

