**Biochemical variables required**

Serum phosphate (as detailed above); vitamin D; parathyroid hormone (PTH); sodium; potassium; cholesterol (total cholesterol, LDL cholesterol, HDL cholesterol); albumin; baseline eGFR and albumin:creatinine ratio.

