**Statistical analysis**

Numerical data will be refined by excluding values beyond physiological limits. Data will be analysed using the statistical package R, with P values <0.05 being regarded as statistically significant. Expert statistical advice will be sought with the aim of using cox regression models to determine the association between serum phosphate and cardiovascular events, adjusting for the known cardiovascular risk factors. Cox proportional hazards multivariate models will also be constructed to provide a time-event analysis. A backwards stepwise elimination of variables approach will help to refine the model and evaluate the contribution of each variable towards the outcome measures.

Ethical considerations

Approval has been sought from the RCGP for the RSC database to be used for such research projects. Our study is retrospective and observational over anonymised patient data. The study involves no clinical interventions, no patient contact and no breach of confidentiality. The results of the study will be submitted for publication to a peer-reviewed journal.

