**Intended output**

Outcome measure 1, 2 or 3 – each outcome requires its own table

|  | Outcome X | | |
| --- | --- | --- | --- |
| *Variable* | *Hazard ratio* | *95% CI* | *p value* |
| Age |  |  |  |
| Gender |  |  |  |
| Ethnicity |  |  |  |
| BMI |  |  |  |
| PDDS |  |  |  |
| Smoking |  |  |  |
| Syst. BP |  |  |  |
| HbA1c |  |  |  |
| Tot chol |  |  |  |
| LDL |  |  |  |
| HDL |  |  |  |
| Albumin |  |  |  |
| **Phosphate** |  |  |  |
| Calcium |  |  |  |
| Vit D |  |  |  |
| PTH |  |  |  |
| Sodium |  |  |  |
| Potassium |  |  |  |
| Albumin:Cr ratio |  |  |  |
| Baseline eGFR |  |  |  |

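### The output template allows one phosphate hazard ratio per outcome, conditioned on whichever of calcium, vitamin D and PTH survive stepwise selection, so a null result cannot be told apart from an association shared with those markers

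*Protocol*

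**What the plan says.** The Background gives the reason for studying the minerals together, "as vitamin D and calcium homeostasis overlap with phosphate regulation", and promises that "the association of these minerals (plus parathyroid hormone) with the three outcomes will be investigated jointly". It adds as literature support that "excess calcium and phosphate or their dysregulation may promote calcification during atherosclerosis". It does not define a joint investigation, and it does not say which marker influences which.

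The Research question is "Is serum phosphate an independent predictor of new atherosclerotic cardiovascular disease events in patients stratified by renal function". The Hypothesis is only that phosphate and cardiovascular risk are related.

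Statistical analysis plans "using cox regression models to determine the association between serum phosphate and cardiovascular events, adjusting for the known cardiovascular risk factors". It then mentions multivariable Cox models and states: "A backwards stepwise elimination of variables approach will help to refine the model". No variable is said to be forced into the model.

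Intended output is headed "Outcome measure 1, 2 or 3 – each outcome requires its own table". Its template has 20 rows, each with one HR, one interval and one p value. Phosphate, calcium, vitamin D and PTH have a row each. There is no second column for a model without the mineral markers.

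Biochemical variables required begins "Serum phosphate (as detailed above); vitamin D; parathyroid hormone (PTH); sodium; potassium; cholesterol". Calcium appears nowhere in that list, although the template has a row for it.

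**The concern.** The text points to two different phosphate estimates. One is adjusted for established cardiovascular risk factors (Statistical analysis, and Limitations through its reference to QRISK2). The other is adjusted for those factors and for the rest of the mineral axis as well (Intended output). The template has room for one, and the protocol does not say which one answers the Research question.

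On the protocol's own account these markers share regulation with phosphate, so the two estimates may differ. A null or attenuated phosphate HR could mean that there is no association, or that the association is shared with calcium, vitamin D or PTH. Stepwise selection adds a second problem: the conditioning set is chosen from the data for each outcome, so phosphate HRs in different tables may not mean the same thing.

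**Working it through.** The protocol has no effect size, event count or power figure on this point, so there is no stated figure to reproduce. The check has three parts.

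**1. What the layout can show.**
- Endpoints: 1 composite + 3 individual cardiac + 3 non-cardiac = 7.
- Mineral covariates beside phosphate: 3, each kept or dropped by elimination, giving 2 × 2 × 2 = 8 possible mineral adjustment sets per endpoint.
- Phosphate HRs reported per endpoint: 1.

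Nothing in the text holds the adjustment set constant across the 7 endpoints.

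**2. How large the shared part could be.** All inputs are assumptions. Let *a* be the slope, in SD of a second marker per SD of phosphate, and *h* the marker's HR per SD. Adding the marker to the model changes the phosphate HR by a factor of about exp(*a* × ln *h*). The last column compares this with an assumed phosphate HR of 1.10 per SD before the marker is added (ln 1.10 = 0.0953).

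| *a* | *h* | *a* × ln *h* | factor | share of ln 1.10 |
|---|---|---|---|---|
| 0.1 | 1.1 | 0.0095 | 1.010 | 10% |
| 0.2 | 1.2 | 0.0365 | 1.037 | 38% |
| 0.3 | 1.3 | 0.0787 | 1.082 | 83% |
| 0.4 | 1.3 | 0.1050 | 1.111 | 110% |

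The last row exceeds the whole effect. It would need a remaining phosphate HR of 1.10/1.111 = 0.99, so it is not used as an upper bound.

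**3. Simulation of the mechanism.** All parameters are again assumptions: 20,000 patients, 10 years, baseline hazard 0.008 per year, 1,593 to 1,670 events, phosphate log HR 0.1 given the second marker (HR 1.105), second-marker log HR 0.2. There was one simulated cohort per cell, and the SE of each log HR was 0.025 to 0.029. If the marker is a mediator, the theoretical total HR is exp(0.1 + 0.2*a*).

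| correlation *a* | theoretical total HR | marker as mediator: without / with marker | marker as confounder: without / with marker |
|---|---|---|---|
| 0.1 | 1.127 | 1.135 / 1.106 | 1.170 / 1.148 |
| 0.3 | 1.174 | 1.144 / 1.070 | 1.118 / 1.054 |
| 0.5 | 1.221 | 1.217 / 1.113 | 1.250 / 1.156 |

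In the mediator case the part lost on adjustment is 0.2*a*/(0.1 + 0.2*a*) of the log HR: 0.02/0.12 = 17%, 0.06/0.16 = 38% and 0.10/0.20 = 50%. In the confounder case the true phosphate HR is 1.105, and the adjusted model is the one that targets it.

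The two set-ups produce the same joint distribution of phosphate, marker and outcome, so differences between the last two columns are sampling noise. Two HRs side by side therefore show how much is shared but not why. One HR alone shows neither.

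**The case against.** The strongest reply is that the plan does what it says. Entering the four markers in one model is an ordinary meaning of a joint investigation, and conditioning on related markers is a fair way to ask whether phosphate predicts independently. If calcium, vitamin D or PTH confound the association, adjustment removes bias and the model without them is the misleading one. The template is only a layout, expert statistical advice is still to be sought, and model sequences are often left to a statistical analysis plan, which is not at hand. Most of this stands. It rules out calling the mineral-adjusted estimate wrong, and it rules out naming either model as the correct one.

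Three stronger readings are tempting, and the documents do not support them.
- A reader might infer that mutual adjustment removes the whole phosphate effect acting through the mineral axis. Only the part carried by the markers actually in the model would go, and only if they lie downstream of phosphate. The protocol states no direction, and elimination may drop any of them.
- A reader might infer that a stated joint calcium-phosphate hypothesis goes untested. The Hypothesis names phosphate alone. The calcification sentence is background, and two separate main effects are compatible with it.
- A reader might infer that an interaction term is required. The template has no row for one, but no section promises one.

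What the reply does not answer is that the layout fixes one phosphate HR per outcome, with an adjustment set left to stepwise selection.

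**Conclusion.** The point holds as a matter of interpretability, not as a demonstrated bias. As laid out, a null phosphate HR cannot be told apart from an association shared with calcium, vitamin D or PTH, and phosphate HRs for different outcomes may be conditioned on different markers. Complete data would not cure either problem.

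The size is unknown from the protocol. With the assumed slopes and marker HRs, excluding the inadmissible top row, the shared factor is 1.010 to 1.082 per SD, or 10% to 83% of an assumed log HR of ln 1.10. This rests on a positive relation between phosphate and the second marker, a harmful marker, and one marker at a time. It illustrates the issue and does not forecast the result.

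The absence of calcium from Biochemical variables required is a plain internal inconsistency and does not depend on any of these assumptions. Overall this is a cheap improvement worth making.

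**What to change.** In Statistical analysis and Intended output, pre-specify for each outcome a fixed sequence with phosphate in every model and no stepwise selection among the mineral markers:

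1. age and sex;
2. plus the cardiovascular risk factors, eGFR and albumin:creatinine ratio, labelled risk-factor-adjusted;
3. plus calcium, vitamin D and PTH, labelled mineral-adjusted.

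Report the phosphate HR and interval from all three side by side, fitted on the same patients so that differences reflect adjustment and not a change of sample. State in the Background that the joint investigation means this comparison, and that it shows how much is shared without establishing direction. Add calcium to Biochemical variables required.

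A phosphate-by-calcium interaction is optional and should be labelled exploratory. In single simulated cohorts of about 1,600 events, true interaction HRs of 1.05, 1.11 and 1.22 were estimated as 0.99, 1.09 and 1.20 (SE of the log HR about 0.025), so a small interaction could easily be missed.

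Cost: two more fits per endpoint (14 over the 7 endpoints), extra columns to explain, and calcium to be extracted. The main downside is a smaller common sample if it is limited to patients with all the mineral tests. The protocol does not say how many that would be.

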**Hypothesis**

There is a relationship between serum phosphate concentration and the risk of cardiovascular event onset.

**Research question**

Is serum phosphate an independent predictor of new atherosclerotic cardiovascular disease events in patients stratified by renal function?

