**Study Design**

This will be a retrospective study of the RCGP-RSC cohort. The data available were collected between April 2005 and March 2015 ([name] to confirm). These will be analysed using Read v2 (5-bit) codes to identify patients by the inclusion and exclusion criteria. Laboratory sample data will be taken from the laboratory sample results collected by GP practices.

Inclusion: One or more serum phosphate measurements recorded before a cardiovascular event (primary myocardial infarction; acute coronary syndrome; revascularisation procedure; ischaemic stroke; peripheral vascular disease; vascular dementia), or recorded in patients without any cardiovascular event in the study period. Patients will be aged 18 years and older.

Exclusion: Patients who have already had primary myocardial infarction; acute coronary syndrome or a revascularisation procedure before any serum phosphate measurements have been recorded. Patients with pre-existing ischaemic stroke, peripheral vascular disease or vascular dementia will also be excluded.

Serum phosphate will be a linear variable or analysed further as a categorical variable by range. ‘Time zero’ will refer to the first available serum phosphate measurement of a patient. The time to any outcome measure will be recorded and associations between serum phosphate and outcomes will be analysed by cox-regression.

In patients where more than one serum phosphate measure is available, the mean average of up to the first five measurements from time zero and before any cardiovascular event will be recorded and used in this study.

Importantly, confounding factors for cardiovascular outcomes in all included patients will form part of this study. For each variable, the selected single measurement will be chosen before the outcome measure and as close to time zero as possible, subject to data availability. The exceptions are baseline eGFR and albumin:creatinine ratio – the mean of two measurements in each case will be taken.

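### The research question is posed by renal stratum, but the planned models and output tables give one pooled phosphate hazard ratio per outcome, with eGFR only as a covariate

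*Protocol*

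**What the plan says.** The Research question section of the protocol asks: "Is serum phosphate an independent predictor of new atherosclerotic cardiovascular disease events in patients stratified by renal function". This is the only place where stratification by renal function appears. The Hypothesis section is general and does not mention the kidney: "There is a relationship between serum phosphate concentration and the risk of cardiovascular event onset".

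Renal function comes up again in three places:

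- **Study Design** treats eGFR and the albumin:creatinine ratio among the confounders. It says only how their baseline values are formed: "the mean of two measurements in each case will be taken".
- **Biochemical variables required** lists "baseline eGFR and albumin:creatinine ratio" without categories.
- **Intended output** gives each of them a covariate row with its own hazard ratio, confidence interval and p value.

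The Statistical analysis section does not mention renal function. It plans Cox models "adjusting for the known cardiovascular risk factors", then says "Cox proportional hazards multivariate models will also be constructed to provide a time-event analysis" and "A backwards stepwise elimination of variables approach will help to refine the model". In the Intended output section "each outcome requires its own table", and that table has a single row for phosphate.

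**The concern.** Adjustment and stratification answer different questions. A main-effects Cox model with eGFR as a covariate assumes the same phosphate hazard ratio at every level of kidney function. It can show whether phosphate predicts events after allowing for eGFR. It cannot show whether phosphate predicts events within each level of renal function, or whether the association differs between levels.

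The distinction matters here because the Background motivates the study with associations reported both in chronic kidney disease and in the general population. Whether phosphate predicts events in each group is a natural reason for putting renal strata into the question. If the strata are chosen only after the pooled result is known, the answer by stratum becomes post hoc.

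**Working it through.** The protocol gives no effect size, event count or renal distribution, so there is no stated figure to reproduce. The main check is a comparison of sections.

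**Step 1. What the question requires.** At a minimum, a phosphate hazard ratio in each renal stratum. A comparison between strata also needs an interaction test.

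**Step 2. What the plan provides.**

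| Section | Treatment of renal function | Phosphate result by stratum? |
|---|---|---|
| Study Design | Mean of two eGFR and two albumin:creatinine values; no groups formed | No |
| Biochemical variables required | Listed as variables; no categories | No |
| Statistical analysis | Not named; adjusted Cox models and backwards elimination | No |
| Intended output | Two covariate rows; one phosphate row per outcome | No |

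**Step 3. Could another meaning of stratified reconcile them?** A Cox model with a separate baseline hazard per renal stratum still returns one phosphate hazard ratio unless an interaction is added. The banded stratifying variable would have no hazard ratio of its own, so the baseline eGFR row could then only hold eGFR as a continuous term within bands. The protocol describes neither bands nor such a term.

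**Step 4. Is adjustment itself assured?** No. The backwards elimination has no stated exception for eGFR, so a final model could contain no eGFR term.

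**Step 5. What pooling could hide (illustration only).** None of the inputs comes from the protocol. Assume two renal groups with equal phosphate variance, hazard ratios per SD of HR_p (preserved function) and HR_r (reduced function), and a share w of events in the reduced group. The information on the log hazard ratio is then roughly proportional to events, so approximately

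pooled HR = exp[(1 − w) ln HR_p + w ln HR_r].

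Example: HR_p = 1.10, HR_r = 1.25, w = 0.2 gives exp(0.8 × 0.0953 + 0.2 × 0.2231) = exp(0.1209) = 1.13.

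| Assumed HR_p | Assumed HR_r | w = 0.1 | w = 0.2 | w = 0.3 | w = 0.5 |
|---|---|---|---|---|---|
| 1.00 | 1.25 | 1.02 | 1.05 | 1.07 | 1.12 |
| 1.10 | 1.25 | 1.11 | 1.13 | 1.14 | 1.17 |
| 1.25 | 1.10 | 1.23 | 1.22 | 1.20 | 1.17 |
| 1.10 | 1.10 | 1.10 | 1.10 | 1.10 | 1.10 |

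In the last row pooling loses nothing. In the first it hides a null effect in one group and a clear one in the other. In the second and third rows, with w = 0.5, opposite patterns give the same pooled value of 1.17. The pooled figure alone cannot tell these cases apart.

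**The case against.** The strongest reply is that this is missing detail and not conflict. The protocol does announce stratification, a statistical analysis plan not at hand may carry it out, and expert statistical advice is still to be sought. Nothing says the models will be fitted only to the whole cohort. The same adjusted model could be run within each stratum, and the table shell repeated. The baseline eGFR row is compatible with that, since continuous eGFR can stay in the model within bands.

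Part of this stands. The absence of eGFR cut-points is not a fault in a protocol, and the eGFR row does not by itself prove pooling. What remains is that the protocol goes beyond silence: it describes an analysis and fixes a table layout, and both treat renal function as a covariate. The advice to be sought is aimed at those same models. An analysis plan faithful to these sections would leave the question without an answer by stratum.

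Three stronger inferences are tempting but not supported:

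- **That the study cannot answer its question.** This is true of the planned output only. eGFR is extracted, so strata and an interaction need no new data.
- **That a pooled hazard ratio describes neither group.** If the effect is similar across renal function, it describes both, and the protocol does not claim that the effect differs.
- **That most of the pooled weight comes from patients with preserved function.** No renal distribution or event split is given. The Limitations section warns that patients with enough blood tests may carry more co-morbidity.

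A hazard ratio of 1.00 with preserved function also sits poorly with the general-population association cited in the Background. It should not be the only case shown.

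**Conclusion.** The point holds as a mismatch between the research question on one side and the Statistical analysis and Intended output sections on the other. As written, each outcome table yields one phosphate hazard ratio, none by renal stratum, and no test of difference; even adjustment for eGFR is not guaranteed. This conclusion rests on the text alone and needs no numerical assumption.

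The practical consequence cannot be sized from the protocol. It depends on whether the effect varies with renal function and on how events split between groups, and the illustration covers outcomes from no loss to serious masking. The pooled analysis still addresses the general hypothesis. The mismatch should be resolved before any outcome analysis, because it touches the only research question and the primary outcome.

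**What to change.** In Statistical analysis: define eGFR bands in advance (the cut-points may sit in the analysis plan), report the phosphate hazard ratio with its 95% confidence interval in each band, specify one phosphate-by-eGFR interaction test for Outcome 1, and keep eGFR in every model whatever the stepwise procedure selects.

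In Intended output: split the phosphate row by eGFR band, or repeat each table by band.

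If stratification is not intended, the simpler course is to reword the research question so that it asks about prediction after adjustment for renal function. eGFR should still be protected from elimination.

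The cost is protocol wording and extra table rows or tables. No new data are needed. Intervals within bands will be wider than the pooled one. Any illustration of masking added to the protocol should be labelled as assumed and shown for several effect pairs, including hazard ratios above 1 in both groups.
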